### Patient and PCP characteristics

For patients with an index visit for LBP during the study period, we will collect information from the EHR on demographic characteristics (e.g., age, gender, race/ethnicity), specific LBP diagnosis (e.g., lumbago, lumbar radiculopathy, lumbar spinal stenosis), comorbid health conditions, and prescription of an opioid or other pain medications in the prior year.

PCPs will be invited to complete an online survey to gather additional information on sociodemographic characteristics (e.g., age, sex, race and ethnicity), pain experiences, attitudes/beliefs regarding chiropractic care, and additional constructs that may predict adoption of chiropractic care. Prior personal experiences of pain and pain treatment may influence PCP management decisions for their patients with LBP. Thus, PCPs will be asked about current or previous personal experiences of musculoskeletal pain including the location(s) and duration of pain. The 3-item PEG Pain Screening Tool will be used to assess their pain on average, how much the pain has interfered with their enjoyment of life, and how much the pain has interfered with their general activity [51]. Each question is scored from 0 to 10 with higher scales indicating worse pain. PCPs will be asked if they have received chiropractic care (yes/no) and, if yes, whether their experience was positive, neutral, or negative. Additionally, we will ask PCPs to self-report patterns of referring to DCs using questions from the National Ambulatory Medical Care Survey [52] including “Have you referred to a chiropractor in the past 12 months?” with participants responding “yes/no” and “How often have you referred your patients to chiropractic care in the past 12 months?” with participants responding “weekly, monthly, quarterly, a few times per year, never”. Attitudes and beliefs towards chiropractic care for LBP will also be captured by adapting questions from previous studies of chiropractic care in primary care [53] and chiropractic experiences among medical students [54]. To understand the acceptability, appropriateness, and feasibility of routine chiropractic care use for LBP among PCPs, we will adapt questionnaires developed by *Weiner et al.*: The Acceptability of Intervention (AIM), Intervention Appropriateness Measure (IAM), and Feasibility of Intervention Measure [55]. Each questionnaire includes four items and a corresponding 5-point Likert scale, allowing responses to range from 1 (strongly disagree) to 5 (strongly agree) for each item. Higher scores indicate greater acceptability, appropriateness, and feasibility [55]. 

### Data analysis

#### Feasibility outcomes

We will use descriptive statistics to summarize the number of months each clinic participated in the study, the number of patients with LBP per month at each site, and the number of each type of PCP recommendation for LBP treatment documented in the EHR. We will describe the provider and patient characteristics using descriptive statistics. Additionally, we will describe whether each of the six implementation strategies was completed for the three participating primary care clinics. We will report on each of the seven dimensions (e.g., temporality, dose) for the six implementation strategies specified in Table 1 as described above.

#### Adoption of chiropractic care and other LBP treatments

Adoption of chiropractic care and other LBP treatments will be presented as the proportion of index visits each month receiving a particular PCP order type. We anticipate that adoption of chiropractic care will be our primary outcome in a future large fully powered cluster randomized trial with other PCP treatment recommendations being important secondary outcomes. The adoption of chiropractic care or other LBP treatments will be illustrated in figures showing the prevalence of orders over the study period.

In the analysis of adoption of chiropractic care, we will create a dichotomous measure “chiropractic referral” (yes/no). We will compare chiropractic referrals before the deployment of the implementation strategy and after deployment begins (i.e., pre-implementation vs. [deployment + follow-up]). The proportion of LBP patients receiving a chiropractic referral for these two time periods will be calculated. The numerator will be those with a chiropractic referral, defined as those LBP patients who received a referral, and the denominator will be all eligible LBP patients. We will use random effects logistic regression adjusting for fixed and random effects at the clinic level and a fixed effect for time of deployment of implementation strategy to estimate the change in the proportion of CHC patients with LBP who are referred to chiropractic care. While main analyses will evaluate initial referrals (i.e., those placed within 21 days of index visit), we will also explore delayed referrals in sensitivity analyses (i.e., referrals placed 22 to 89 days following index visit).

The above analyses will then be repeated to evaluate changes in other LBP treatments over the study period. We will compare the proportion of LBP patients who are referred to other nonpharmacologic treatments (e.g., PT, acupuncture), prescribed pain medications (e.g., opioids), referral to imaging (e.g., MRI), or referral to medical specialist (e.g., sports medicine, orthopedics). We will also identify interventional procedures for LBP (e.g., epidural injections, surgery) documented in the EHR during the study period.

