### Patient population

During the fourteen-month study period, we will identify all patients aged 18 or older who have a diagnosis of LBP documented in the EHR by their PCP at a participating clinic. This will include acute or chronic LBP with or without leg pain using appropriate ICD codes (e.g., M54.5, M54.1, M54.16, M54.41, M54.42, M54.31, M54.32, M48.06, M48.07, M51.16, M51.17, M99.83, S33.5) [36]. We will exclude patients with a red flag diagnosis suggesting serious pathology may be the cause of LBP (e.g., cauda equina syndrome, cancer, spine infection or fracture). We will also exclude patients who had a primary care visit for LBP within the prior 90 days. Thus, patients with LBP may enter our study more than once if they have a new episode of LBP with 90 days between primary care visits.

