### Adoption of chiropractic care and other treatments

Adoption of chiropractic care will be measured through PCP referrals to chiropractic care. We will extract this information from the EHR based on orders placed following an index visit with a PCP for LBP. The rate of adoption for a given month will be the proportion of index visits where an order for chiropractic care is placed within 21 days. This period of time is based on a recent study showing that most patients receive at least one order within 21 days of an initial visit to their PCP for acute LBP and that orders after 21 days are uncommon [12]. This study also found that < 5% of participants with acute LBP received an order to chiropractic care within 21 days [12]. Additionally, we will identify other recommendations documented in the EHR by PCPs within 21 days of the index visit. These will include: (1) other evidence-based nonpharmacologic treatments (e.g., acupuncture, massage, physical therapy); (2) prescribed pain medications (e.g., NSAIDs, opioids); (3) referral to imaging (plain x-rays, MRI), or referral to specialists (e.g., sports medicine, orthopedics) who may offer interventional procedures (e.g., epidural injections, surgery).

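### Adoption is defined per index visit in one place and per patient in the before/after comparison, although patients may enter more than once

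*Protocol article*

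**What the plan says.** All references are to the protocol article.

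- **Measurement, *Adoption of chiropractic care and other treatments*:** the monthly adoption rate is "the proportion of index visits where an order for chiropractic care is placed within 21 days". The unit is the index visit.
- **Data analysis, *Adoption of chiropractic care and other LBP treatments*, first paragraph:** adoption "will be presented as the proportion of index visits each month receiving a particular PCP order type". The unit is again the index visit.
- **Same section, second paragraph:** for the comparison of pre-implementation with deployment plus follow-up, "The proportion of LBP patients receiving a chiropractic referral for these two time periods will be calculated". The numerator is "defined as those LBP patients who received a referral" and "the denominator will be all eligible LBP patients". The unit is now the patient.
- **Methods part of the abstract:** it also speaks of a proportion of patients, tied to 21 days after their index visit.
- **Patient population:** "patients with LBP may enter our study more than once if they have a new episode of LBP with 90 days between primary care visits".
- **Model (same second paragraph):** a random effects logistic regression with fixed and random effects at clinic level and a fixed effect for time of deployment. No patient-level term is named.

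**The concern.** The two definitions coincide only if every patient enters once, and the article allows re-entry. The paragraph that sets the before/after contrast is also the one that switches unit. A programmer could follow either definition and claim to have followed the protocol.

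Each choice has its own consequence. Counting patients once per phase gives a longer phase more chances to record at least one referral. Counting entries removes that problem but puts several correlated records from one patient into the model.

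The monthly figures and the phase comparison may then not reconcile. The same analysis is to be repeated for other nonpharmacologic care, pain medication, imaging and specialist referral, so the ambiguity reaches every adoption outcome.

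**Working it through.** The article gives no sample size, power or expected effect, so there is no such figure to reproduce. Its timeline agrees with itself: 4 + 2 + 8 = 14 months at the first clinic.

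**Phase lengths** (Study design; a new clinic starts every two months), before/after in months: first clinic 4/10, second 6/8, third 8/6. The totals are 4 + 6 + 8 = 18 and 10 + 8 + 6 = 24 clinic-months.

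**Reading A: each patient counted once per phase, as referred if any index visit led to a referral.**

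Assumptions, none of them in the article:
- The referral probability is constant at p = 5% per index visit, so there is no effect. The article cites a rate under 5% in acute LBP.
- First entries are spread evenly over the phase.
- Each further full 90 days left in the phase brings a new entry with probability r = 0.15 or 0.30.
- Months have 30 days, and clinics are weighted by phase length.

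For a patient with k further 90-day intervals left, P(ever referred) = 1 − (1 − p)(1 − rp)^k.

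| k | r = 0.15 | r = 0.30 |
|---|---|---|
| 0 | 5.00% | 5.00% |
| 1 | 5.71% | 6.43% |
| 2 | 6.42% | 7.83% |
| 3 | 7.12% | 9.21% |

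Shares of patients with k = 0, 1, 2, 3:
- 4 months: 0.75, 0.25, 0, 0
- 6 months: 0.50, 0.50, 0, 0
- 8 months: 0.375, 0.375, 0.25, 0
- 10 months: 0.30, 0.30, 0.30, 0.10

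Example, r = 0.15:
- 4 months: 0.75 × 5.00 + 0.25 × 5.71 = 5.18%
- 10 months: 0.30 × (5.00 + 5.71 + 6.42) + 0.10 × 7.12 = 5.85%

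| Clinic (months before/after) | r = 0.15 | r = 0.30 |
|---|---|---|
| First (4/10) | 5.18% → 5.85% (+13%) | 5.36% → 6.70% (+25%) |
| Second (6/8) | 5.36% → 5.62% (+5%) | 5.71% → 6.24% (+9%) |
| Third (8/6) | 5.62% → 5.36% (−5%) | 6.24% → 5.71% (−8%) |
| Pooled, weights 4:6:8 and 10:8:6 | 5.43% → 5.65% (+4%) | 5.87% → 6.30% (+7%) |

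A second recurrence model was simulated, again with no effect and p = 5%. The gap between entries was 3 months plus an exponential time with mean 3 months. If 20% of index visits come from recurrent patients, the spurious odds ratio is 1.08 in the first clinic and 0.97 in the third. If 50% do, it is 1.25 and 0.92. The pattern is the same.

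**Reading B: each entry counted.** The expected proportion under no effect is p in every phase, whatever its length (5% and 5%). What remains is correlation within patients. A rough guide for repeats within one phase is the design effect 1 + (m − 1)ρ, with m entries per patient and within-patient correlation ρ, both assumed:
- m = 1.2, ρ = 0.1 to 0.5: 1.02 to 1.10
- m = 2, ρ = 0.1 to 0.5: 1.10 to 1.50

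**The case against.** The strongest answer is that the article uses patient and index visit interchangeably and means patient entries throughout. Several features support this. Main-analysis referrals are those within 21 days of the index visit. Delayed referrals run from day 22 to day 89, just short of the 90-day re-entry threshold. The Table 3 footnote on patient-level characteristics measures them at the index visit. The feasibility analysis counts patients per month. This is an episode-based structure, and under it the phase-length effect vanishes. The point stands as a reason not to assert that effect as fact. It does not remove the contradiction, because the paragraph that defines numerator and denominator says patients and never says entries.

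A reader might infer three stronger things:

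- **That the comparison is biased by phase length.** The article nowhere says that a patient is counted once as ever referred in the phase. The shift holds only on that reading.
- **That repeat entries are treated as independent.** This would be read from the model terms named. Independence is not stated, and a separate analysis plan could add a patient-level term.
- **That both consequences apply together.** They largely belong to opposite readings. Counting once per phase collapses repeats within that phase. Under that reading, correlation remains only for patients seen in both phases.

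It is also fair to say that the re-entry rate is assumed, that +25% is one clinic at the upper assumed rate, and that the trial is a three-clinic pilot which declares itself underpowered for adoption outcomes.

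**Conclusion.** The inconsistency of unit is in the current text and should be resolved. Its consequence depends on which unit was meant.

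On the literal per-patient wording, and with no change in provider behaviour, the pooled before/after proportion rises by about 4% to 7% relative. That is 0.2 to 0.4 percentage points on a base a little above 5% (5.65 − 5.43 = 0.22; 6.30 − 5.87 = 0.43). The first clinic moves up by 13% to 25% and the third down by 5% to 8%. These figures rest on the assumed 15–30% re-entry per further 90 days and scale with it. Re-entry is plausible because chronic LBP is included, but the article gives no rate.

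On the per-entry reading there is no such shift, and what remains is within-patient correlation that the named model terms do not cover. This is probably small if few patients re-enter.

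A shift of this size is unlikely to change a feasibility conclusion. The point still merits correction because the study aims to show that adoption can be measured, and because this definition carries forward to the anticipated primary outcome of the future trial.

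**What to change.** Use the index visit (episode) as the single unit in the abstract, in the Measurement section and in the Data analysis section on adoption:

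- **Numerator:** eligible index visits with a chiropractic order within 21 days.
- **Denominator:** all eligible index visits in the phase.
- **Other outcomes:** the same unit for the delayed-referral sensitivity analysis and for the other LBP treatments.

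State how repeat entries by the same patient are handled, for example by a patient-level random intercept or by a sensitivity analysis restricted to each patient's first index visit. Nesting patients within PCP is not required. If repeats are too few, at a low referral rate, to estimate a patient intercept well, the first-visit analysis is the practical choice.

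The cost is a few sentences, slightly more analysis work and possibly slightly wider intervals. No new data are needed, provided that entries by the same patient can be linked in the EHR extract, which the 90-day exclusion already requires.

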## Methods

### Study design

We will use a stepped-wedge cluster randomized controlled pilot trial design to evaluate the feasibility of an implementation strategy designed to increase adoption of chiropractic care for LBP. A stepped-wedge design allows each clinic to receive the implementation strategy, with the pre-implementation period acting as the control [34]. Three primary care clinics at CHCs will be randomized to receive the implementation strategy first, second, or third over a fourteen-month study period as shown in Fig. 1. Clinic randomization will be overseen by a biostatistician. At our first clinic, we will have a four-month pre-implementation period, a two-month implementation deployment period, and a subsequent eight-month follow-up period. We will stagger the start of our implementation strategies, beginning in a new clinic every two months. The study protocol was approved by the Boston University Medical Campus IRB. We will conduct parallel qualitative interviews throughout the study period with PCPs, staff, and DCs to help understand if proposed strategies are perceived as feasible within local CHCs. PCPs, DCs, and administrative staff participating in surveys and in-depth interviews will provide consent via an online survey. A waiver of consent was approved for collection of patient demographic information and PCP orders for LBP from the Electronic Health Record (EHR). Reporting will be consistent with the Standards for Reporting Implementation Studies (STaRI) statement [35]. 

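### The adoption model names no calendar-time term and leaves its one time-like term undefined, so a secular trend in referrals would pass into the pre/post estimate

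*Protocol article*

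**What the plan says.** Study design (protocol article): three clinics are "randomized to receive the implementation strategy first, second, or third over a fourteen-month study period". The section describes the control condition as follows: "A stepped-wedge design allows each clinic to receive the implementation strategy, with the pre-implementation period acting as the control". For the first clinic, "we will have a four-month pre-implementation period, a two-month implementation deployment period, and a subsequent eight-month follow-up period"; the other clinics follow at two-month steps ("beginning in a new clinic every two months").

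Data analysis, Adoption of chiropractic care and other LBP treatments: referral is a yes/no outcome, compared between the pre-implementation period and deployment plus follow-up combined. The change in the referred proportion is to come from "random effects logistic regression adjusting for fixed and random effects at the clinic level and a fixed effect for time of deployment of implementation strategy". The same analysis is then repeated for other nonpharmacologic treatments, pain medications, imaging and specialist referral.

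Calendar time appears elsewhere only descriptively, as monthly proportions and figures over the study period. The Discussion says the pilot is underpowered for effectiveness on adoption outcomes. No significance level or hypothesis test is stated.

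**The concern.** In a stepped wedge every clinic moves from control to strategy and none moves back, so exposed months are later months. The randomised stagger exists to separate the two: while some clinics have started and others have not, the clinics still waiting show what time alone is doing. The analysis uses that information only if the model contains a calendar-time effect. Without one, each clinic is compared with its own earlier self, and any change over 14 months in coding, EHR use, season or insurance is counted as the strategy's effect.

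At stake is the estimate for the outcome the article expects to be primary in a later full-scale trial, and the parallel estimates for opioids, imaging and other care. More index visits would not help: they narrow the interval around the wrong value.

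**Working it through.** The plan gives no sample size, power or effect figure to reproduce. The check rebuilds the schedule and asks what the stated model estimates when the strategy does nothing.

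**1. Schedule (from Study design).** Three clinics, 14 months, deployment starting in months 5, 7 and 9.

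| Clinic | Pre months | Mean | Post months | Mean | Gap |
|---|---|---|---|---|---|
| First | 1–4 | 2.5 | 5–14 | 9.5 | 7 |
| Second | 1–6 | 3.5 | 7–14 | 10.5 | 7 |
| Third | 1–8 | 4.5 | 9–14 | 11.5 | 7 |

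That is 4 + 6 + 8 = 18 control and 10 + 8 + 6 = 24 exposed clinic-months. Only months 5–8 (4 of 14) contain both exposed and control clinics.

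**2. What the time term can mean.**
- *Pre/post indicator.* This is the exposure itself, so nothing adjusts for time.
- *Each clinic's start month.* It is constant within clinic and aliased with clinic fixed effects: intercept, two clinic indicators, exposure and start month make five columns of rank 4. With a random clinic intercept alone it could be fitted, but it would still not describe change within a clinic.
- *Time since deployment, zero beforehand.* It describes growth of the effect, and there is still no calendar term.
- *Study month or period.* This would adjust for trend, but the text does not say it. Signed months from deployment, negative beforehand, would with clinic intercepts be study month in another coding; that is not stated either.

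**3. Bias under the first reading.** With clinic intercepts and no time term, a linear trend on the log-odds scale passes into the exposure coefficient as about 7 × (monthly trend). With a true odds ratio of 1.00 and assumed monthly trend odds ratios:
- 1.02^7 = 1.15
- 1.03^7 = 1.23
- 1.05^7 = 1.41

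As a second illustration, let referral drift from 2% to 4% between months 1 and 14. The log-odds are −3.892 and −3.178, a rise of 0.714 over 13 intervals. Then exp(0.714 × 7/13) = 1.47, which matches a logistic fit to expected counts. A fall from 4% to 2% gives 0.68, so the bias can go either way. Adding a linear month term or month effects returns the odds ratio to 1.00.

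**4. Clinic entered twice.** Read literally, the three clinics carry both fixed and random effects. In a direct likelihood check, with assumed clinic differences of −0.4, 0 and +0.5 on the logit scale, the likelihood peaked at a random-intercept variance of zero. The odds ratio stayed at 1.47 whatever the variance. The random term is redundant and is not the source of the trend bias. With a random intercept only, the bias remains (about 1.39 in the same 2% to 4% scenario).

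**5. Precision cost of adjusting.** With equal weight per clinic-month, the variance of the exposure coefficient is proportional to 1/(residual sum of squares of the exposure indicator).
- Clinic only: 4×10/14 + 6×8/14 + 8×6/14 = 9.714; variance 1/9.714 = 0.103.
- Plus linear month: the within-clinic month sum of squares is 3 × 14 × (14² − 1)/12 = 682.5 and the cross-product is 7 × 9.714 = 68. The residual is 9.714 − 68²/682.5 = 2.939; variance 0.340.
- Plus seven two-month periods: 2 × [12 − 50/7 − 32/3 + 144/21] = 2.095; variance 0.477.

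Standard-error ratios: √(0.340/0.103) = 1.82 and √(0.477/0.103) = 2.15.

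**The case against.** The strongest reply is that this is one condensed sentence in an article. It defines the pre/post contrast first and then lists what the model adjusts for, so the time term may be a loosely worded study-period effect in addition to exposure. That is possible, and it is why the point cannot be put as proof that the investigators intend no calendar adjustment. But the article does state its adjustment set, the words describe deployment rather than study time, and no other section supplies a calendar term. If study period was meant, the sentence still has to say so.

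Several stronger readings are tempting and are not supported:
- *Entering clinic twice causes the trend bias.* It does not (step 4). The phrase may also mean clinic-level covariates plus a random intercept; the notes to Table 3 mention clinic-level characteristics.
- *A biased estimate will size the future trial.* The article says only that adoption is the anticipated primary outcome there. Its stated aim here is the feasibility of measuring adoption.
- *The trial has an inflated type I error.* Simulated false-positive rates for the 2% to 4% drift were 13%, 25% and 50% at 20, 50 and 100 index visits per clinic-month, against 4–5% with a linear month term. They rest on assumed drift, assumed volume and a two-sided 5% test that the protocol never specifies, so they are illustrative only.
- *A PCP random intercept is required.* It may be sensible, since PCPs place the orders, but it is a separate and optional choice.

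It is also fair that the absolute shifts may be small. At an assumed 3% baseline, odds ratios of 1.15 and 1.23 are about 0.4 and 0.7 percentage points. The planned monthly figures might reveal a marked trend, but they do not adjust the estimate.

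**Conclusion.** The point holds as one of specification. The model as stated names no calendar-time effect, and its only time-like term is undefined. Under three of the four readings it yields either a comparison open to secular trend or a term that cannot be identified alongside fixed clinic effects. Fitted as a pre/post contrast with clinic effects, the estimate is an uncontrolled before/after comparison that does not use the randomised stagger.

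The 7-month gap follows from the documented schedule alone. The size of the bias does not: odds ratios of 1.15 to 1.41 assume a log-linear trend of 1.02 to 1.05 per month, roughly even visit volume and no true effect, and the documents give neither trend nor volume. Because this is a three-clinic feasibility pilot that calls itself underpowered, with no test or decision rule attached to the estimate, the grade is should-fix.

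**What to change.** Rewrite the model sentence so that it:
- names the exposure term: pre-implementation versus deployment plus follow-up;
- adds a fixed calendar-time effect, either two-month periods or a linear month trend, with the other as a sensitivity analysis and the main choice fixed in advance;
- enters clinic once, as fixed intercepts for the three clinics;
- reports the change in proportion with its confidence interval as descriptive. Three clinics allow only 3! = 6 orderings, so the smallest one-sided permutation p-value is 1/6;
- applies the same model to the other LBP treatments.

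On the choice of time term: period categories can follow seasonal or irregular change, which a straight line cannot. But with few referrals, a period containing none would have no finite estimate. A random intercept for PCP may be added if wanted.

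The cost is analysis wording only, since the month of each index visit is already needed for the planned monthly proportions. The price is precision: the standard error of the exposure effect rises about 1.8-fold with a linear month term and 2.2-fold with two-month periods. That loss reflects how little of the schedule (months 5–8) has exposed and control clinics side by side.
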